### Data and safety monitoring

In order to assess possible changes in risk/benefit ratio to study subjects and to obtain independent oversight of study conduct, an external Data and Safety Monitoring Board (DSMB) will be established to oversee the progress of the study. The DSMB will be composed of representatives from statistics, nephrology and endocrinology. External DSMB study reviews will be conducted after half of the participants (n = 30) have completed all study procedures. The DSMB will review and monitor the study procedures and potential risks with a focus primarily on safety. Serious Adverse Events (SAEs) will be reviewed by the DSMB members in order to determine whether additional safety measures should be initiated. There are no predefined criteria for stopping the study, although the DSMB may recommend changing study drug concentration or stopping the study based on SAE or 25OHD data. If there are significant deviations from major study assumptions, the DSMB or study investigators may choose to evaluate 25OHD levels and stop the study early.

The principal investigator and his co investigators will be responsible for maintaining and assessing subject safety in the study, monitoring the presence and severity of adverse events, and monitoring compliance with study drug use. Information on adverse events will be obtained by laboratory findings, including 25OHD, ionized calcium and urine calcium:creatinine levels.

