### Randomization, blinding and stratification procedures

We will use a computer-generated randomization sequence. Only the CHEO pharmacy will have access to the randomization sequence and will be responsible for participant randomization and allocation. Only the pharmacist will know the identity of the study drug administered to specific patients. Given the expected recruitment (two to three per month) and potential impact of season on 25OHD, randomization will be performed in permuted blocks (four within each stratum). We will blind patients, families, investigators, hospital staff, and research personnel to treatment arm. Blinding was considered necessary to avoid (i) families altering the outpatient dose and (ii) a number of secondary outcome measures are that are potentially subjective (echocardiography, timing of extubation, need for fluids or catecholamine infusion). Within each age group, the two interventions will be indistinguishable (vial, volume, color, taste, consistency and smell).

Participants will be stratified into whether or not they are expected to receive at least 8 weeks of study drug prior to surgery. This stratification should guarantee that an equal number of CHD patients who will not receive 8 weeks of oral dosing end up in both the high and low dose arms. We will further stratify by age (under or over 1 year of age).

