**Fig. 1 Fig1:**
[figure not shown]
Flow chart of study-related procedures and measurements. Patients and/or caregiver may decline initiation blood work and urine samples and still participate. Postoperatively, urine will only be collected at PICU admission if it was not collected in the operating room. Participants with isolated postoperative hypercalciuria will only have renal ultrasound at the request of nephrology. CHD, congenital heart disease; PICU, Pediatric Intensive Care Unit; POD, postoperative day

**Table 4 Tab4:** Biochemical measurements on research specimens

Sample	Timepoint				
	Pre-treatment^a^	During study drug administration^b^	Preoperative^c^	Operating room prior to surgery	Postoperative
Blood	Vitamin D^d^	Vitamin D^d^	Vitamin D^d^	Vitamin D^d^	Vitamin D^d^
		Ionized calcium	Ionized calcium	Ionized calcium	Ionized calcium
				VDBP	VDBP
				PTH	PTH
				Immune function	Immune function
				(for example, cathelicidin)	(for example, cathelicidin)
				Immune activity	Immune activity
				(for example, cytokines)	(for example, cytokines)
Urine	Calcium to	-	-	Calcium to	Calcium to
	Creatinine ratio			Creatinine ratio	Creatinine ratio

^a^neonates, or < 2 months of supplement anticipated

^b^any patient who receives > 6 months of supplement

^c^all outpatients who receive > 2 months of supplement

^d^25OHD will be measured to indicate vitamin D status. The 25OHD level determined at the time of standard preoperative blood work, for safety purposes, will be ordered through the laboratory. The intraoperative and postoperative 25OHD measurements will be determined, using LC-MS/MS technology that adheres to and meets the standards of the Vitamin D External Quality Assessment Scheme

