#### During period of study drug administration

All outpatient participants will have blood collected at the time of standard presurgical blood work (2 to 3 weeks prior to surgery) for both 25OHD and ionized calcium. These samples are collected to ensure that patients do not go for surgery with potentially toxic levels of vitamin D. The safety officer will review the ionized calcium level on the patients chart, and follow up if required, as per the safety measures outlined in the sections below. For those participants who will receive the study drug for more than 6 months, we will measure 25OHD and calcium, and they will also have additional blood work to ensure that potentially toxic levels are not maintained for long periods prior to surgery. The timing of this blood work will not be specified and will occur as part of clinically indicated blood work during regularly scheduled clinic appointments

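### The article blinds investigators and hospital staff but bases investigator-led safety monitoring partly on 25OHD and withholds 25OHD from no blinded role, so outpatients with a presurgical sample can be partly unblinded

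*Protocol article*

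**What the plan says.** All references are to the protocol article.

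- **Randomization, blinding and stratification procedures:** "We will blind patients, families, investigators, hospital staff, and research personnel to treatment arm". Two reasons are given: families might change the outpatient dose, and several secondary outcomes (echocardiography, extubation timing, fluids, catecholamines) are open to judgment.
- **Data and safety monitoring:** the principal investigator and co-investigators "will be responsible for maintaining and assessing subject safety in the study, monitoring the presence and severity of adverse events", and compliance as well. The next sentence names the sources: "Information on adverse events will be obtained by laboratory findings, including 25OHD, ionized calcium and urine calcium:creatinine levels".
- **Table 4, footnote d:** "The 25OHD level determined at the time of standard preoperative blood work, for safety purposes, will be ordered through the laboratory". A separate LC-MS/MS stream covers the samples taken during and after surgery.
- **During period of study drug administration:** outpatients have 25OHD and ionized calcium drawn 2 to 3 weeks before surgery. "The safety officer will review the ionized calcium level on the patients chart". Children on study drug for more than 6 months have a further 25OHD.
- **Intraoperative biological samples and measurements:** operating-room 25OHD is frozen and assayed at study end. Operating-room urine results stay off the hospital chart but go to the study investigator as well as the safety officer.
- **Safety measures and clinically relevant research findings:** the safety officer identifies and contacts participants with high calcium or vitamin D. A standard operating procedure and Additional file 3, neither of which is shown, give further detail.

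**The concern.** The article assigns blinding and safety monitoring to the same people, and one of the named monitoring data sources is the concentration that the study drug is meant to change. The preoperative value becomes available before surgery, hence before every postoperative outcome. The article has an off-chart rule for operating-room urine and delayed assay for operating-room 25OHD, but neither safeguard is stated for the presurgical 25OHD.

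At stake are the outcomes for which blinding was thought necessary. The Co-interventions section also relies partly on blinding as its reason for not protocolizing postoperative care, so a leak weakens that reason. Adequacy of blinding is itself a feasibility outcome for the phase III trial, and a result-routing problem would distort what the pilot says about it.

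**Working it through.** The article gives no figure for unblinding. The check asks how well one preoperative 25OHD value separates the arms on the article's own forecasts.

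**Inputs** (Perioperative 25OHD levels): 80% of high dose at or above 90 nmol/L, with a mean of 130–150; 40–50% of usual care at or above 90. Allocation is taken as 1:1. These forecasts come from studies in healthy children and are assumed to hold at the presurgical sample.

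**Step 1, no SD needed.** Guess high dose at or above 90 nmol/L and usual care below it.

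- Proportion correct = [P(≥90 | high) + P(<90 | usual)] / 2.
- Usual care 40%: (0.80 + 0.60)/2 = 0.70. Usual care 50%: (0.80 + 0.50)/2 = 0.65.
- P(high | ≥90) = 0.80/(0.80 + 0.40) = 0.67, or 0.80/(0.80 + 0.50) = 0.62.
- P(usual | <90) = 0.60/(0.60 + 0.20) = 0.75, or 0.50/(0.50 + 0.20) = 0.71.

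**Step 2, cross-check.** With normal distributions and a common SD, the two rates fix the standardized difference and the SD cancels. The correct-guess rate is Φ((0.842 + 0.253)/2) = 0.71 with usual care at 40%, and Φ(0.842/2) = 0.66 at 50%. This agrees with Step 1.

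**Step 3, high values, with assumed SDs.** The high-dose SD is set so that 80% exceed 90: (130 − 90)/0.842 = 48, up to (150 − 90)/0.842 = 71. The usual-care SD is not given and is assumed to be 20–40 nmol/L.

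| 25OHD value | High dose | Usual care |
|---|---|---|
| above 150 nmol/L | 34–50% | 0.1–7% |
| above 200 nmol/L | 7–24% | at most 0.3% |

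In the least revealing case, P(high | >150) = 0.337/(0.337 + 0.067) = 0.83 and P(high | >200) = 0.070/(0.070 + 0.003) = 0.96. Over the whole range of these SDs, the best achievable accuracy is 0.68–0.84.

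**Step 4, who is exposed.** The text describes the presurgical sample for all outpatients; Table 4, footnote c, limits it to outpatients with more than 2 months of supplement. Children having surgery within 2 months have no further research blood until the operating room. The Duration of study drug section expects 75–80% of patients to receive more than 2 months, or 62 × 0.75 to 62 × 0.80, about 47 to 50 children. This is an upper figure, because only outpatients are sampled.

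**The case against.** The strongest reply is that the article never says in words that investigators receive each child's 25OHD. The sentence on laboratory sources is passive, individual high values are assigned to the safety officer, and the article separately allows the DSMB or the investigators to choose to look at 25OHD if major assumptions fail. That option would be odd if they saw the values routinely. Only ionized calcium is expressly placed on the chart, and the laboratory is not called the hospital's. The procedure and flow diagram that are not shown may settle the routing.

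Much of this stands. A reader might infer that every child's 25OHD appears on the hospital chart, that investigators routinely read it, or that families are told the level. The article states none of these. The only contact it describes with participants over results is by the safety officer for elevated values.

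A reader might also infer that the value reveals the arm, and might reach a correct-guess rate of 69–81% by assuming an SD of 40 with means of 130–150 against 80–90. That SD puts Φ(40/40) = 84% to Φ(60/40) = 93% of the high-dose arm above 90 nmol/L, where the article forecasts 80%. The distributions overlap, and the article's rates support 65–70%.

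The conflict itself survives. The text that is shown gives blinded investigators a monitoring duty and names 25OHD as a source for it, with no restriction. A supplementary procedure that masked the value would still leave that wording to be corrected.

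**Conclusion.** The sections on blinding and on safety monitoring conflict as written, and no stated rule withholds 25OHD from blinded roles. The consequence is partial unblinding: about 65–70% correct arm identification from one value, against 50% by chance, in outpatients with the presurgical sample. The figure rests on the article's forecasts, on 1:1 allocation and on the value reaching someone who is meant to be blinded. That values above 200 nmol/L are close to conclusive rests further on the assumed SDs and normality.

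The effect is confined to the subjective secondary outcomes, the postoperative co-interventions and the feasibility assessment of blinding. A reader might extend it to the primary result, but that is an LC-MS/MS concentration in a postoperative sample and is little open to assessor judgment. The sample size is not affected.

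**What to change.** Reconcile the sections on blinding, Table 4 (footnote d), sampling during study drug administration, intraoperative samples, data and safety monitoring, and safety measures by adding one rule. Individual 25OHD results before database lock go only to the safety officer and the DSMB and are kept off the chart. State that the safety officer takes no part in outcome assessment, which the article does not now say.

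Amend Data and safety monitoring so that investigators receive adverse events, calcium and any action triggered under the existing safety rules, but not the 25OHD value. The operating-room urine procedure is a model only for its off-chart rule, since those results still go to the study investigator. The existing thresholds and actions need no change.

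The cost is wording and laboratory routing. With 62% of the target enrolled at the time of writing (0.62 × 62, about 38 children), the change can protect about 24 still to be enrolled, as well as any enrolled children not yet sampled. There are two small downsides. Treating clinicians do not see 25OHD unless the safety officer acts on it, and a triggered action may itself hint at the arm in a few children. Under the assumed SDs, values above 200 nmol/L would occur in at most 31 × 0.07 to 31 × 0.24, about 2 to 7 high-dose children, if all were sampled.

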### Safety measures and clinically relevant research findings

A flow diagram depicts the safety measures in place and response to clinically relevant research findings for individual study participants (Additional file 3). A standard operating procedure has been developed for adherence to the following safety measures.

To avoid vitamin D overdose, hypercalcemia and side effects, we have selected a supplement level recently proven to be safe in healthy children and will target the period of high-dose supplementation to 6 months and no more than 12 months. Study participants with elevated blood calcium and/or vitamin D levels will be identified and contacted by the safety officer. For 25OHD, although 500 nmol/L is generally considered the definitive acute toxicity threshold, we have chosen to intervene with 25OHD levels above 200 nmol/L as this value is supraphysiological and exceeds our study goal. The following details the actions that will be taken with abnormal values:For 25OHD above 200 nmol/L with evidence of hypercalcemia (vitamin D toxicity), discontinue study drug immediately, repeat the values (fasting), and refer to endocrinology.For 25OHD above 200 nmol/L without hypercalcemia, the study drug will be reduced by 50 %; (c) For 25OHD above 250 nmol/L, without hypercalcemia: study drug will be discontinued.For hypercalcemia with 25OHD under 200 nmol/L, repeat the bloodwork (fasting) and refer to endocrinology.

Both postoperative hypo- and hypercalcemia will be managed by the clinical team as required. Study participants with persistently elevated blood calcium levels (for more than 2 days, not explained by intravenous calcium administration) will be referred to endocrinology (Additional file 3).

As prolonged exposure to hypercalciuria (>3 months) could theoretically cause nephrocalcinosis, we will have ultrasounds performed prior to hospital discharge on all patients with elevated immediate preoperative urine calcium to creatinine ratios. Any study participant with nephrocalcinosis will be referred to the nephrology service for further assessment.

Participants that have study drug discontinued or decreased will be retained in the study, have perioperative biological samples collected as outlined, and will be included in the analysis using intention to treat methodology.

## Discussion

Research by our group and others has documented not only that 4 out of every 5 CHD patients have inadequate blood levels of vitamin D following surgery, but an association between immediate postoperative hormone levels and clinical course [22, 25, 26]. Altogether, these findings and similar results in adult critical care and CHD surgery populations, suggest that optimization of vitamin D status following CHD repair could lessen inflammation, reduce nosocomial infection and improve cardiac function [11, 13–17, 43–45]. As an inexpensive medication (approximately $15/month) that is generally regarded as safe, vitamin D has the potential to be an ideal intervention for improving outcomes following CHD repair. As protocols and guidelines should be evidenced-based, well-designed clinical trials are essential to adjust clinical practice. This trial aims to determine whether a preoperative proposed dosing strategy will be sufficient to elevate preoperative 25OHD and prevent postoperative vitamin D deficiency. Further clinical study will be required to investigate how normalization of vitamin D levels impacts the clinical course of patients with CHD requiring cardiac surgery.

### Trial status

At the time of writing, 62 % of the target sample size had been enrolled and the anticipated study completion date is January 2016.

## Abbreviations used

AI: Adequate Intake
CHD: congenital heart disease
CPB: cardiopulmonary bypass
DSMB: data safety monitoring board
RCT: randomized controlled trial
RDA: recommended dietary allowance
PICU: Pediatric Intensive Care Unit
PTH: parathyroid hormone
SAE: severe adverse event
UL: tolerable upper intake level
VDBP: vitamin D binding protein
1,25(OH)2D: 1,25 dihydroxyvitamin D
25OHD: 25 hydroxyvitamin D.
